## Abstract

**Background:**

Diabetic patients show an increased prevalence of non-dipping arterial pressure pattern, target organ damage and elevated arterial stiffness. These alterations are associated with increased cardiovascular risk.

The objectives of this study are the following: to evaluate the prognostic value of central arterial pressure and pulse wave velocity in relation to the incidence and outcome of target organ damage and the appearance of cardiovascular episodes (cardiovascular mortality, myocardial infarction, chest pain and stroke) in patients with type 2 diabetes mellitus or metabolic syndrome.

**Methods/Design:**

**Design**: This is an observational prospective study with 5 years duration, of which the first year corresponds to patient inclusion and initial evaluation, and the remaining four years to follow-up.

**Setting**: The study will be carried out in the urban primary care setting.

**Study population**: Consecutive sampling will be used to include patients diagnosed with type 2 diabetes between 20-80 years of age. A total of 110 patients meeting all the inclusion criteria and none of the exclusion criteria will be included.

**Measurements**: Patient age and sex, family and personal history of cardiovascular disease, and cardiovascular risk factors. Height, weight, heart rate and abdominal circumference. Laboratory tests: hemoglobin, lipid profile, creatinine, microalbuminuria, glomerular filtration rate, blood glucose, glycosylated hemoglobin, blood insulin, fibrinogen and high sensitivity C-reactive protein. Clinical and 24-hour ambulatory (home) blood pressure monitoring and self-measured blood pressure. Common carotid artery ultrasound for the determination of mean carotid intima-media thickness. Electrocardiogram for assessing left ventricular hypertrophy. Ankle-brachial index. Retinal vascular study based on funduscopy with non-mydriatic retinography and evaluation of pulse wave morphology and pulse wave velocity using the SphygmoCor system. The medication used for diabetes, arterial hypertension and hyperlipidemia will be registered, together with antiplatelet drugs.

**Discussion:**

The results of this study will help to know and quantify the prognostic value of central arterial pressure and pulse wave velocity in relation to the evolution of the subclinical target organ damage markers and the possible incidence of cardiovascular events in patients with type 2 diabetes mellitus.

**Trial Registration:**

ClinicalTrials.gov Identifier: NCT01065155

## Background

The estimated prevalence of type 2 diabetes mellitus (DM2) in the industrialized world is 6-8% [1]. The prevalence of the disease is expected to increase in the coming years as a result of the increase in life expectancy in developed countries, and as a consequence of changes in life style in the developing world. It has been estimated that the number of diabetics will double over the next 25 years. As a result, by the year 2030, Spain can be expected to have over three million diabetic patients [1,2]. Cardiovascular diseases are the main causes of mortality among diabetic patients [3]. The incidence of coronary mortality in DM2 patients is four times greater than in the general population [4,5]. On the other hand, the prevalence of arterial hypertension (AHT) in DM2 is practically twice as high as in the non-diabetic population. Thus, 50-60% of all DM2 patients are hypertensive, and this percentage increases with age and the presence of nephropathy [6-8]. AHT in the diabetic patient is usually systolic [9-12], its control poses greater difficulties [13,14], and the nocturnal dip in pressure is smaller [15]. Moreover, the concomitant presence of both conditions (AHT and DM2) increases cardiovascular morbidity-mortality - with an increased incidence of coronary, cerebrovascular, and peripheral vascular disease, renal failure, heart failure and diabetic retinopathy, and a greater risk of death due to cardiovascular disease [16].

Clinical blood pressure (CBP) measurement remains the standard of reference, and has been a key element in predicting cardiovascular disease, but there is increasing evidence that home blood pressure (HBP) measurement by the patient, and particularly ambulatory blood pressure monitoring (ABPM), shows a stronger correlation to target organ damage and cardiovascular events [17-20]. The prognostic value of nocturnal blood pressure (BP), and particularly of the nocturnal decrease or dip in systolic blood pressure (SBP), seems to be greater than that of diurnal BP. Individuals with a lower nocturnal fall in BP have a greater prevalence of target organ damage and a less favorable outcome [21,22].

The presence of target organ damage increases the risk of clinical cardiovascular complications in DM2. In this context, left ventricular hypertrophy (LVH), assessed according to electrocardiographic criteria, increases the risk of coronary complications and stroke [23]. Silent worsening of renal function, reflected by increased creatinine levels, a drop in glomerular filtration rate (GFR), or an increase in protein excretion in urine, increase the risk of cardiovascular diseases [24,25]. Pathological ankle-brachial index (ABI) values show very good correlation to the development of coronary complications, the incidence of stroke, and cardiovascular mortality [26]. In addition, a number of prospective studies have shown carotid artery intima-media thickness (IMT) to be an independent risk factor for both coronary disease and stroke [27]. An increased IMT and/or the detection of atheroma plaques are associated with an up to four-fold increase in the relative risk of clinical complications of arteriosclerosis [28].

On the other hand, the evaluation of major artery stiffness is gaining importance as an indicator, since it is one of the main determining factors of the general condition of blood circulation [29,30]. Arterial stiffness is determined via two systems: pulse wave velocity (PWV)(time from arrival of the pulse wave to the carotid artery and femoral artery) and applanation radial tonometric pulse wave analysis for calculating aortic pressure, as well as the relationships between the latter and the peripheral pressure values [31-33]. Increased arterial stiffness or diminished arterial distensibility determined by pulse pressure implies increased cardiovascular risk. On the other hand, there is evidence that diabetes predisposes to premature vascular aging.

Considering the need in diabetic patients to better establish the prognostic value of central arterial pressure and pulse wave velocity in relation to the evolution of the target organ damage markers (left ventricle growth indicators, renal damage markers (microalbuminuria and diminished glomerular filtration), retinal damage and vascular markers (IMT of the carotid artery and ABI)) and the possible incidence of cardiovascular events in DM2 patients, an observational prospective study involving annual follow-up over at least four years is contemplated.

### The following objectives have been established

To evaluate the prognostic value of central arterial pressure and pulse wave velocity in relation to the incidence and outcome of renal (microalbuminuria, diminished glomerular filtration and the appearance of terminal renal failure), cardiac (LVH) and vascular damage (IMT and ABI), retinal vascular impairment, and the appearance of cardiovascular episodes (cardiovascular mortality, ischemic heart disease and stroke) in patients with DM2.

## Methods/Design

### Study design

An observational prospective study with a duration of 5 years, of which the first year corresponds to patient inclusion, and the remaining four years to follow-up. A minimum of 5 visits are contemplated, comprising a baseline visit at the time of patient inclusion in the study, and annual follow-up visits.

The study was approved by an independent ethics committee from the University Hospital of Salamanca (Spain), and all participants signed an informed consent document.

### Setting

The study will be carried out in the rural primary care setting, in the research unit of La Alamedilla primary care center, to which the general practitioners from two primary care centers serving a population of 46,000 inhabitants send patients for the evaluation of possible target organ damage and vascular risk.

### Study subjects

Consecutive inclusion will be made of the patients referred to the research unit and who meet the corresponding inclusion criteria, i.e., patients diagnosed with DM2 and aged 20-80 years, with none of the following exclusion criteria: patients unable to comply with the protocol requirements (psychological and/or cognitive disorders, failure to cooperate, educational limitations and problems for understanding written language, failure to sign the informed consent document), patients participating or who will participate in a clinical trial during the study, and patients with serious comorbidities representing a threat to life over the subsequent 12 months.

The sample size has been calculated to determine the time the patients take in suffering an event - the latter being interpreted as morbidity-mortality or the appearance of new target organ damage. To this effect, two groups will be considered, classified according to the median central arterial pressure value. The study accepts an alpha risk of 0.05 and a beta risk of 0.30 in two-sided contrasting for the detection of a minimum difference in relative risk between the two groups of ≥ 2.5 points, and considering an events rate within the high central arterial pressure group (values above the median) of 35% at the end of the study period. A total of 52 patients are required in each group, estimating a loss to follow-up of 10%. A final total of 110 patients therefore will be included.

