### Statistics analysis

A first descriptive analysis will be made of the sociodemographic and clinical characteristics of the study groups. The data will be presented with the mean and 95% confidence interval in the case of quantitative variables, and as frequency distributions for qualitative variables. The Pearson chi-squared test will be used to analyze associations between qualitative variables. The Student t-test for independent samples will be used to compare the means for the two arterial pressure groups. In turn, the analysis of repeated measures will be based on the McNemar test for qualitative data and the Student t-test for paired data in application to quantitative data.

Survival will be analyzed with the Kaplan-Meier and actuarial methods on each visit and at the end of follow-up. The log-rank test will be used for comparing survival in the two groups. Lastly, a Cox regression model will be developed to estimate the event risk between the groups, adjusting for the possible confounding variables analyzed in the study.

Hypothesis contrasting will establish an alpha risk factor of 0.05 as the limit of statistical significance. The SPSS/PC+ version 15.0 statistical package will be used (SPSS Inc., Chicago, Illinois, USA).

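### The enrolment target of 110 does not follow from 52 per group and 10% loss, whether 52 is taken before or after loss; the effect on power is small

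*Protocol article*

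**What the plan says.** All the figures stand in the second paragraph of Study subjects in the protocol article.

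- Groups: "two groups will be considered, classified according to the median central arterial pressure value", so two halves of equal size.
- Error rates: "The study accepts an alpha risk of 0.05 and a beta risk of 0.30 in two-sided contrasting", that is, 70% power.
- Effect: "detection of a minimum difference in relative risk between the two groups of ≥ 2.5 points".
- Event rate: "considering an events rate within the high central arterial pressure group (values above the median) of 35% at the end of the study period".
- Group size and loss: "A total of 52 patients are required in each group, estimating a loss to follow-up of 10" per cent.
- Enrolment: "A final total of 110 patients therefore will be included".

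The abstract repeats the 110. The paragraph introduces the calculation as one for time to an event, but names no formula. Statistics analysis plans a log-rank comparison of the two groups and then a Cox model.

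**The concern.** The last two sentences of the paragraph present 110 as the result of a stated group size and a stated loss. The inputs and the result are all printed, so this is not a detail lost in condensing a longer document: a reader can redo the step, and it does not come out.

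The number recruited rests on this paragraph. Anyone judging whether the study was adequately sized, or whether the loss seen in follow-up was within plan, needs to know how many evaluable patients were required and how much loss 110 was meant to absorb. As written, neither can be recovered. The target power is only 70%, so there is little slack, and it is worth checking whether the slip matters for power.

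**Working it through.** **Inputs (Study subjects).** Two-sided alpha 0.05 (z = 1.960); beta 0.30 (z = 0.524); high-group risk 0.35; relative risk 2.5; equal groups; loss 10%. Derived, not stated: low-group risk 0.35/2.5 = 0.14, difference 0.21, mean risk 0.245.

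**Step 1: reproduce 52.** The pooled two-proportion formula without continuity correction is

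n = [1.960·√(2·0.245·0.755) + 0.524·√(0.35·0.65 + 0.14·0.86)]² / 0.21²

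= (1.192 + 0.309)² / 0.0441 = 51.1, so 52 per group. No loss allowance is in this figure.

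**Step 2: from 52 to 110, if 52 is evaluable.**

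- Dividing by the retained fraction: 104/0.9 = 115.6, so 116.
- The cruder multiplication: 104 × 1.1 = 114.4, so 115.
- Loss that 110 covers: 1 − 104/110 = 5.5%.
- Patients left from 110 after 10% loss: 110 × 0.9 = 99, against 104 required.

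**Step 3: if 52 already contains the loss.** The total is 2 × 52 = 104, not 110. The net number is 52 × 0.9 = 46.8, about 47 per group.

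**Step 4: can the second reading be excluded by its inputs?** No. The two-proportion formulas need more than 47 evaluable per group at 70% power: 48.7 (unpooled), 49.6 (arcsine), 51.1 (pooled). A log-rank calculation can, however, reach 52 after loss:

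- With exponential survival, 35% versus 14% implies a hazard ratio of ln 0.65 / ln 0.86 = 2.86.
- Schoenfeld events: 4·(1.960 + 0.524)² / (ln 2.86)² = 22.4, so 23.
- Patients: 23 / (2 × 0.245) = 46.9 per group net.
- Multiplying by 1.1 gives 51.6, so 52 per group.

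The figure 52 can therefore arise either before or after loss, depending on the formula. The figure 110 follows in neither case.

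**Step 5: power for 35% versus 14%.**

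| Evaluable per group | Pooled | Unpooled | Arcsine | Schoenfeld (hazard ratio 2.86) |
|---|---|---|---|---|
| 47 (52 less 10%) | 66.3% | 68.5% | 67.7% | 71.2% |
| 49.5 (110 less 10%) | 68.6% | 70.7% | 70.0% | 73.4% |
| 52 | 70.8% | 72.8% | 72.1% | 75.5% |

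With 110 enrolled and 10% lost, power lies between 1.4 points below the planned 70% and 3.4 points above it.

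**The case against.** The strongest reply is that the sentence attaches the 10% to the 52, so 52 includes the loss and 110 is a loose rounding up from 104. Step 4 shows that a log-rank calculation on the article's own inputs supports this, and the paragraph does speak of time to event. On that reading 110 is generous: 94 evaluable patients are needed, and 110 could absorb 1 − 94/110 = 14.5% loss. This part stands: it cannot be asserted that 52 is the number before loss, nor that 116 is the only right total. It does not rescue the text, because 110 is still presented as the result of a calculation that ends at 104.

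Another possible route to 110 is the unpooled 48.7, rounded to 49 and divided by 0.9, which gives 54.4, so 55 per group. The stated requirement would then have to be 49, not 52.

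It can also be said that Study limitations concedes a small sample for end events and points to a multicenter analysis of 800 patients. That is a fair disclosure about size, but it does not explain or correct the 110.

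Two stronger readings are tempting and are not supported:

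- A reader might infer a material loss of power because the planned analysis is a Cox model with 2.5 as its hazard ratio. The article states a relative risk alongside a cumulative event rate at the end of the study. Taking 2.5 as a hazard ratio replaces the stated effect with a smaller one.
- A reader might infer a further loss from the Cox model "adjusting for the possible confounding variables analyzed in the study". The article attaches no power to that model and gives no figure for how strongly confounders relate to the pressure grouping. An unadjusted log-rank comparison is planned as well, and sizing on an unadjusted contrast is common practice.

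**Conclusion.** The point holds as an error of derivation. From 52 per group and 10% loss the total is 116 (115 by the cruder multiplication) if 52 is evaluable, and 104 if 52 includes the loss. The printed 110 is neither, and no other section repairs it.

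The consequence is small. On the first reading the study enrols 6 fewer than its own inputs require (116 − 110) and covers 5.5% loss instead of 10%. On the second it enrols 6 more than the total implied (110 − 104). With 99 evaluable patients, power is about 69% by the pooled formula and about 70% or slightly more by the others. This rests on a low-group risk of 14%, derived from reading 2.5 as a risk ratio, and on loss falling equally on the two groups. It does not support a claim that the study is materially underpowered against its own 70% target.

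**What to change.** Keep 110 and correct the paragraph in Study subjects so that the figures agree. It should state:

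1. the formula used;
2. whether 52 is before or after loss;
3. whether 2.5 is a risk ratio or a hazard ratio;
4. how much loss 110 allows for.

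If 52 is the evaluable number, wording such as this would do: *52 evaluable patients per group are required; 110 enrolled allows for 5.5% loss; with 10% loss 99 remain, with power of about 69–70% for the unadjusted comparison.* If 52 already includes the loss, say so, give the net number and the formula that produced it, and describe 110 as a total above the calculated 104.

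The cost is rewording only: no extra patients, visits or analyses. On the first reading the stated power becomes very slightly less favourable.

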### Measurements

#### Sociodemographic variables and cardiovascular risk factors

Patient age, sex, race, educational level and occupational status. Hypertension, dyslipidemia, alcohol consumption, smoking, physical activity and a history of premature cardiovascular disease (before 55 years of age in males and before 65 in females) in first-degree relatives.

#### Cardiovascular diseases

Coronary events: Myocardial infarction, unstable angina, stable angina, coronary revascularization. Cerebrovascular events: Ischemic stroke, intracranial hemorrhage, transient brain ischemia. Hospital admissions due to heart failure. Symptomatic peripheral arterial disease: Claudication over a distance of less than 100 m, resting pain, amputation. Heart failure. Atrial fibrillation.

#### Treatment variables

Treatment for diabetes. Antihypertensive treatment. Lipid-lowering treatment. Antiplatelet treatment.

#### Anthropometric measurements

Body weight is to be determined on two occasions using a homologated electronic scale (Seca 770) following due calibration (precision ± 0.1 kg), with the patient wearing light clothing and no shoes. These readings will be rounded to 100 g. Height in turn will be measured with a portable system (Seca 222), recording the average of two readings, and with the patient shoeless in the standing position. The values will be rounded to the closest centimeter. Body mass index (BMI)(kg/m^2^) will be calculated. Waist circumference will be measured using a flexible graduated measuring tape with the patient in the standing position without clothing. The upper border of the iliac crests are located, and the tape is wrapped around above this point, parallel to the floor, ensuring that it is adjusted without compressing the skin. The reading is taken at the end of a normal breath according to the recommendations of the 2007 SEEDO Conference [34].

#### Laboratory parameters

Lipids, creatinine, glucose, high-sensitivity C-reactive protein (CRP), fibrinogen and glycosylated hemoglobin (HbA1c) in blood and microalbuminuria. The parameters will be measured on a blind basis in the reference laboratory after patient fasting for at least 8 hours.

#### Office or clinical blood pressure

Office blood pressure measurement involves three measurements of systolic (SBP) and diastolic blood pressure (DBP), using the average of the last two, with a validated OMRON model M7 sphygmomanometer (Omron Health Care, Kyoto, Japan), by following the recommendations of the European Society of Hypertension [35]. Pulse pressure (PP) will be estimated with the mean values of the second and third measurements.

#### Home blood pressure (HBP)

This parameter will be measured using an OMROM model M7 sphygmomanometer (Omron Health Care, Kyoto, Japan). Three measurements will be made in the morning (between 6:00 and 9:00 a.m.), and three in the afternoon/evening (between 18:00 and 21:00 p.m.), over a period of 7 days, with a minimum interval of one minute between measurements, and excluding the first measurement in each case and the values corresponding to the first day of measurement [36]. The investigator will instruct the patients on how to perform the blood pressure recordings at home. Written instructions will be provided, as well as a self-registry sheet, to ensure correct pressure monitoring.

#### Ambulatory blood pressure monitoring (ABPM)

The ABPM was performed on a day of standard activity, with an adequate cuff for the size of the patient's arm. A control system, SpaceLabs 90207 model (Spacelabs Healthcare, Issaquah, Washington, USA), validated according to the protocol of the British Hypertension Society, was used [37]. The records in which the percentage of valid readings was ≥66% of the total and with valid readings at all times were considered to be valid. Furthermore, for the records to be evaluable, at least 14 measurements were required during the daytime period, or at least seven during the nightime or rest period. The monitor was scheduled for obtaining blood pressure measurements every 20 min during the daytime period and every 30 min during the rest period. The average and dispersión estimators of SBP and DBP were calculated during the 24-h, daytime and nightime periods, defined based on the diary reported by the patient. The patient completes a form specifying bedtime and wake-up time.

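### The ABPM evaluability rule joins its day and night minimums with 'or', so a record with fewer than seven night readings can still feed the night and 24-h averages

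*Protocol article*

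**What the plan says.** The ABPM section of the Protocol article sets two layers of acceptance.

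- **Validity.** A record is valid if "the percentage of valid readings was ≥66% of the total and with valid readings at all times".
- **Evaluability.** A second sentence opens "Furthermore, for the records to be evaluable" and adds the minimum counts: "at least 14 measurements were required during the daytime period, or at least seven during the nightime or rest period".

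Readings are scheduled "every 20 min during the daytime period and every 30 min during the rest period". The average and dispersion of systolic and diastolic pressure "were calculated during the 24-h, daytime and nightime periods, defined based on the diary reported by the patient". The section gives no rule that withholds one period's average when that period's count is too low. It also does not say what unit of time the coverage phrase in the validity rule refers to.

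**The concern.** An analyst who programs the rule as printed will accept any record with 14 daytime readings, however few night readings it has, provided the validity rule is met. Night and 24-h averages would then be calculated for that record.

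Night pressure is the ABPM quantity that the rationale stresses. The Background states: "Individuals with a lower nocturnal fall in BP have a greater prevalence of target organ damage and a less favorable outcome". It also suggests that night pressure may predict better than day pressure. So the period left without an effective minimum is the one of most interest. The explorations are repeated yearly, so the number of readings behind a patient's night average could also vary from visit to visit.

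**Working it through.** **Inputs from the ABPM section:** 3 readings per hour by day, 2 per hour at rest, the 66% threshold, and the minimums of 14 (day) and 7 (night).

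**Assumptions:** a 24-h recording; the 66% is taken of scheduled readings; the minimums count valid readings. The length of the rest period comes from each patient's diary and is not given, so 5 to 10 h is shown.

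**Step 1. Does the 66% rule protect either period?** With a night of *h* hours, day = 3 × (24 − *h*), night = 2 × *h*, total = day + night, and needed = 0.66 × total, rounded up. The last column is needed − night: the fewest day readings a record can have and still reach 66%.

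| Night (h) | Day | Night | Total | Needed | Day alone | Fewest day readings |
|---|---|---|---|---|---|---|
| 5 | 57 | 10 | 67 | 45 | 85.1% | 35 |
| 6 | 54 | 12 | 66 | 44 | 81.8% | 32 |
| 7 | 51 | 14 | 65 | 43 | 78.5% | 29 |
| 8 | 48 | 16 | 64 | 43 | 75.0% | 27 |
| 9 | 45 | 18 | 63 | 42 | 71.4% | 24 |
| 10 | 42 | 20 | 62 | 41 | 67.7% | 21 |

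Daytime alone exceeds 66% in every row, so the percentage rule sets no floor on night readings. In the other direction, any record that reaches 66% has at least 21 day readings, more than the 14 required. The daytime half of the 'or' is then always met, and under these assumptions the second sentence, read literally, excludes no record that has passed the first.

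**Step 2. Does the coverage phrase supply the missing night minimum?** Its meaning is not stated, so take the two natural readings.

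- *At least one valid reading in each period.* With an 8-h night, 42 day + 1 night = 43 of 64 = 67.2%. The record passes both layers. Its night average is a single value, and night dispersion cannot be estimated.
- *At least one valid reading in each hour.* The night then has at least as many readings as hours. From 7 h upward that is seven or more, and the day has at least 14, so both minimums are met. A 6-h night can pass with 6 (38 day + 6 night = 44 of 66 = 66.7%) and a 5-h night with 5 (40 day + 5 night = 45 of 67 = 67.2%). Both fall below seven.

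**Step 3. The rule with 'and'.** With an 8-h night, an evaluable record would have at least 7 of 16 scheduled night readings and at least 14 of 48 day readings, on top of 43 of 64 overall.

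**The case against.** The strongest reply is that the two sentences are cumulative. The opening words of the second add to the validity rule and do not replace it. A reader might infer from the 'or' that a record with no night readings at all can be evaluable. The document does not support that: such a record lacks valid readings at all times, whether this means every hour or every period. This part of the reply stands.

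A reader might also infer that the rules contradict each other. They do not. Under hourly coverage, with nights of 7 h or more, the minimum counts are redundant, and both rules can be applied together.

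It can further be said that 'or' was meant distributively, each minimum governing its own period. That is plausible, the more so because the literal reading leaves the sentence with nothing to do. The field manuals mentioned under Quality control may handle this. But the printed text has no rule per period, and the distributive reading does not say what happens to the 24-h average when the night falls short. This reply explains the wording without removing the need to correct it.

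Finally, no planned inference is shown to depend on the rule. ABPM is not named in the objectives, the groups are split at median central arterial pressure, and the Cox model refers only in general terms to confounders among the study variables. This stands and limits the weight of the point.

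**Conclusion.** The point holds in a limited form. As printed, the rule can accept records that miss the protocol's own night minimum and still calculate night and 24-h averages from them. The shortfall depends on how the undefined coverage phrase is read: down to one night reading if it means one per period, or 5 to 6 readings in 5- to 6-h nights if it means one per hour. If it means hourly coverage and nights last 7 h or more, nothing is lost.

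These counts follow from the stated schedule and the assumed length of the night. They do not show how often such records will occur. A reader might want a bias in mmHg, but the documents do not support a figure. They give no day-night difference, and the Background says the nocturnal fall is smaller in diabetic patients. A figure based on an empty night would describe a record that the coverage phrase excludes.

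This is a minor data-quality point. It affects ABPM-derived values, wherever they are reported or used as covariates. The objectives, the central-pressure grouping and the power are unaffected.

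**What to change.** Either replace 'or' with 'and', so that an evaluable record needs both the 14 daytime and the seven night readings in addition to the 66% rule, or apply each minimum to its own period's average and set the night and 24-h values to missing when the night minimum is not met. The second option keeps the daytime average of a record with a poor night.

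In either case, define the coverage phrase, for example as at least one valid reading in every hour.

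The cost is one word and one definition. A few more recordings, or their night and 24-h values, would count as non-evaluable.
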